### vi) Specific scientific questions

1.  *Safety and immunogenicity of PCV under an accelerated 1-2-3 month schedule in PNG infants*

PCV has been shown to be safe and efficacious against IPD in SA infants given at 6-10-14 weeks of age ([name], pers comm). The standard PNG immunization schedule is at 1-2-3 months of age to achieve optimal vaccine coverage. PNG infants have higher Pnc carriage rates than reported in SA infants, which may affect immune responses to PCV. It is important that the reactogenicity and immunogenicity of PCV be established in this population at 1-2-3 months of age in comparison to control infants receiving the standard PNG infant immunizations. The response in SA infants after 1 and 2 doses of PCV at 6 and 10 weeks respectively suggests that fewer than 3 doses may be necessary in some populations (43). Therefore antibody responses to 1 and 2 doses will be examined. Immunogenicity will be primarily assessed by serotype-specific serum IgG at 2, 3 and 4 months of age, in comparison to responses in infants not receiving PCV.

2. *Safety and immunogenicity of neonatal immunization with PCV in PNG infants and comparison with early infant immunization*

Should infants be able to mount appropriate immune responses to PCV in the first week of life, then neonatal PCV should result in earlier protection against IPD due to vaccine serotypes and may provide protection against early carriage. Though neonatal responses to PCV may appear modest because of maternal antibody present, conjugate vaccines may still prime for memory (36). For our primary outcome, serum Pnc serotype-specific IgG antibody at age 2 months will be compared between neonatal PCV and control groups. This will assess whether there is a booster antibody response to the second dose of PCV in the neonatal group compared to infants given their first dose at 1 month of age and to naturally acquired antibody levels in the control group. This will determine whether neonatal PCV results in earlier protection, and monitoring will show whether safety has been compromised. We note that a safe and equally immunogenic outcome would be a more favourable response to neonatal PCV, since neonatal administration has the major logistic advantage of increasing uptake of the vaccine in the population.

*3. Induction of immunologic memory by neonatal and early infant PCV in PNG infants*

PNG infants remain at ongoing risk of IPD in the first 5 years of life. Long-term protection induced by PCV depends on the successful priming for immunologic memory so infants can mount brisk anamnestic antibody responses on subsequent challenge. All infants will receive 23-valent PPV at 9 months of age (6 months after their primary course) to evaluate the induction of memory to PCV serotypes. These serotypes in PPV are not immunogenic in PNG infants at age 9 months (except for 23F) (24) so that significant IgG responses to PCV serotypes compared to PCV-naive controls will indicate the induction of memory. This vaccine is efficacious from age 6 months and provides some cover against serotypes which are important causes of IPD in this population. Antibody avidity maturation (post-primary to post-booster immunization) will also be assessed as it is a surrogate marker for the induction of memory after conjugate vaccines (39, 80, 81) and influences the functional capacity of antibodies produced (35). Avidity maturation will be assessed by comparing changes in avidity index between 4-, 9- and 10-month samples in comparison to controls. Antibody persistence will be evaluated with blood samples at 18 months of age.

*4. The impact of neonatal versus early infant vaccination upon nasal carriage of pneumococci*

Reduction in the burden of early Pnc carriage in the critical neonatal period may have an important impact on early disease as well as the development of long-term immunity to Pnc infections. Regular carriage sampling in the first month of life will assess the impact of neonatal PCV immunization, and carriage will be assessed at regular intervals thereafter to determine persisting effects of PCV on carriage compared to controls.

*5. The impact of early colonisation with vaccine serotypes on antibody responses (systemic and mucosal) to neonatal and early infant immunization with PCV*

In the Asaro Valley 60% of infants acquired Pnc in the URT by 15 days of age. PCV serotypes are responsible for 59% of carriage isolates in the first 3 months of life in PNG (16). Swabs will be collected at weekly intervals during the first month to identify children with early ( 2 weeks) colonisation. This will allow evaluation of the effects of early colonisation on systemic antibody responses to subsequent PCV immunization. Effects of time of colonisation and PCV on mucosal immunity (salivary IgA responses to Pnc CPS and OMPs) will also be assessed .

6. The relationship between the capacity to respond to Pnc antigens and developmental factors controlling postnatal maturation of immune competence

(a) Development of natural immunity to Pnc antigens

Humoral immunity will be assessed as serum IgG and salivary IgA responses to CPS and Pnc OMPs at regular intervals, and cellular immunity as in vitro Th1/Th2 cytokine production. In this initial assessment of natural immunity, we will focus on the study group who do not receive PCV. Serological assays for measuring serum and salivary antibody responses to Pnc CPS and OMPs established in our laboratory will provide detailed information on the ontogeny of humoral Pnc systemic and mucosal immunity in this high-risk population.

Our forerunner T-cell studies on a cohort of 130 subjects (64, 65) have demonstrated that the kinetics of postnatal cytokine response capacity is highly variable amongst Australian infants, and in particular Th1 response capacity is slow to develop over the first 18 months of life. Moreover, development of this function appears to be rate-limiting in relation to competence to respond to vaccines, and may be similarly related to competence to resist infection (65). Comparable data of this nature are not available from similar-sized cohorts of infants in third world countries, where the overall levels of microbial exposure are much higher. It is now accepted that microbial exposure during infancy constitutes the principal stimulus for postnatal maturation of Th1 function and it is possible that Th1 functions in PNG infants may mature much faster, due to the higher levels of environmental microbial stimulation. We propose to resolve this important question via analysis of generalised (and Pnc‑specific) immunity in the PNG cohort, compared with data from the Perth cohort (64, 65).

(b) Development of PCV-induced T‑cell immunity to Pnc antigens

Based on experience from studies on Australian infants, we will seek to ascertain whether quantitative and qualitative aspects of vaccine-induced Pnc CPS and carrier protein‑specific immunity are directly related to the underlying capacity to transcribe cytokine genes in polyclonal-induced responses, and/or whether vaccine response capacity is related to kinetics of maturation of cells of the innate immune system (in particular, IL‑12 responses). Studies on Perth children also suggest that aspects of the functional capacity of cord blood mononuclear responses are predictive of subsequent immunological reactivity during infancy (82), and on this basis the proposed PNG analyses will also include cord blood functions and how these relate to subsequent postnatal maturation of immune competence including responsiveness to PCV.

Our previous findings indicated a strong Th2‑bias in early vaccine responses, and relative instability in Th1 memory up to 18 months of age (64, 65). In relation to vaccine design, this argues for considering the use of stronger (Th1-trophic) adjuvants to boost vaccine responses in this age range. However, the parallel situation with respect to vaccine responsiveness in infants in a third world setting is largely undefined, and different strategies may need to be considered for improvement of vaccine efficacy in such populations. Information relevant to this important issue can be readily obtained in this study by comparing data on tetanus-specific T‑cell responses in PNG infants to those found in the earlier Perth study. These data will also be employed in relation to assessment of vaccine safety (see 8 below).

(c) Colonisation with Pnc

We will additionally test the possibility that variations in the functional competence at birth of cells of the innate and adaptive arms of the immune system may influence susceptibility to colonisation with Pnc during the immediate postnatal period. A variety of evidence from our group and others derived from studies on cord blood cells (83) suggests that delayed/attenuated functional maturation of Th1‑associated effector mechanisms during foetal life may result in some individuals being in a transient state of “developmental immunosuppression” in early infancy, relative to the population at large. This subgroup will potentially respond to environmental antigens less efficiently than the population average. We will assess polyclonal T‑cell function and innate immune function in cord blood cells from PNG infants, and relate these data to subsequent patterns of Pnc colonisation and manifestations of natural and vaccine-induced immunity to Pnc, to ascertain whether these outcomes are influenced by immune status at birth.

*7. Early carriage of Pnc as a potential cause of impaired responses to vaccine and non-vaccine Pnc antigens*

We will seek to define the relationship between the timing of nasal colonisation with Pnc and (i) the kinetics of acquisition of natural and vaccine-induced Pnc‑specific immunity, and (ii) the Th1/Th2 balance within these responses. Of particular interest will be the possibility that early colonisation with Pnc in the neonatal period may induce a form of “tolerance” associated with priming of Th2-polarised immunity to Pnc‑antigen(s), which may in turn modulate host capacity to develop natural or vaccine-induced immunity to Pnc.

8. Assessment of immunological safety of neonatal immunization with PCV in PNG infants

(a) Possible interference with immune responses to concomitant vaccines (DTP and measles)

Similar to concerns with early onset Pnc carriage, neonatal immunisation with PCV may result in preferential Th2 priming for the PCV carrier protein CRM197 which may affect subsequent responses to the virtually identical DT component of DTP vaccine. The potential for non-specific interference with responses to two additional “index” vaccines, the TT component of DTP vaccine which elicits a mixed Th0‑like response in infants which includes a strong Th2 component (64, 65), and the measles vaccine which elicits a response with a stronger Th1 component, will also be assessed. T‑cell cytokine responses to all these vaccines will be measured in the three study groups, to ascertain in particular whether neonatal PCV modulates the Th1/Th2 balance in host responses. Antibody responses to concomitant TT, Hib (PRP-TT) and DT will be measured at 4 months of age to ensure that there has been no interference with humoral immune responses. In this population all children achieve protective anti-tetanus and anti-diphtheria toxin antibodies after 3 doses of ActHib (76).

*(b)* *Non-specific interference with normal maturation of the immune system, in particular Th1 immunity*

Given the important role of microbial stimulation in driving the postnatal maturation of immune function(s), it is theoretically possible that PCV, particularly if given in the neonatal period, may contribute to this drive and hence accelerate the normal maturation process. This represents a possible safety issue, as (for example) precocious postnatal maturation of Th1 function may pose potential risks for inflammatory disease. Alternatively, PCV may promote non-specific Th2 immunity and delay Th1 maturation resulting in increased susceptibility to infectious and allergic diseases. Accordingly, specific analyses will be performed to contrast the kinetics of postnatal maturation of Th1/Th2 response capacity in groups with and without neonatal PCV.

*9. The impact of PCV on respiratory morbidity in PNG infants in the first year of life*

Asaro Valley infants on average suffer 3 ALRI episodes in the first year of life (84). To ensure the safety of neonatal or early PCV and any potential benefits of PCV on respiratory morbidity, there will be close monitoring of infants by trained field staff throughout the study using established methods. Though this proposed study is complete in itself, we intend to continue to follow up participants after completion of the study at age 18 months to ensure ongoing safety in terms of respiratory morbidity, hospitalisation and death.

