**Aims of the Study**

In Papua New Guinea (PNG), there is an early onset of dense bacterial carriage in the upper respiratory tract (URT) and a high pneumococcal (Pnc) disease burden in the first year, especially under 6 months of age. This study aims to investigate a number of important, unanswered questions that are critical to evidence-based vaccine intervention:

1. Is immunization with pneumococcal conjugate vaccine (PCV) safe and immunogenic in PNG infants, when administered according to the standard immunization schedule in PNG (1-2-3 months)?
2. Does neonatal immunization with PCV provide a more favourable antibody response in early childhood than immunization starting at 1 month of age, without compromising safety?
3. Does neonatal or early infant immunization with PCV induce immunologic memory to the relevant Pnc polysaccharides?
4. Does neonatal or early infant immunization with PCV affect nasopharyngeal carriage of vaccine and non-vaccine serotypes?
5. What is the impact of early colonisation with vaccine serotypes on antibody responses (systemic and mucosal) to neonatal or early infant immunization with PCV?
6. Is the response of PNG infants to Pnc antigens governed by developmental factors controlling postnatal maturation of immune competence?
7. Is there evidence that early carriage of Pnc leads to tolerance or impaired responses to vaccine or non-vaccine Pnc antigens?
8. With respect to immunological safety of neonatal immunization with PCV in PNG infants :
9. Does neonatal immunization with PCV interfere with humoral and cellular immune responses to concomitant vaccines (diphtheria toxoid, tetanus toxoid and measles)?
10. Does PCV interfere with normal maturation of the immune system, in particular Th1 functions which mature rapidly during infancy?
11. Does PCV reduce the incidence of respiratory morbidity in PNG infants in the first year of life?

In addition, the study will provide a more detailed immunologic evaluation of pneumococcal polysaccharide vaccine (PPV) in the first year of life and will re-establish demographic surveillance within a field site ready for an efficacy study of neonatal immunization, if justified by the results of the present study, or for the evaluation of other candidate pneumococcal vaccines.

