**vii) Sample size requirements**

**Urban Rural n**

Group #2 #3 #1 #2 #3 #1 312

Block 1 13 13 13 13 52

Block 2 13 13 26 13 13 26 104

Blocks 3-4 26 26 26 26 26 26 156

The block randomisation schema is set out above. The sample size requirements were based on the primary questions and assumed 80% power and a 5% significance level. Distributions of published Pnc vaccine responses (21, 43, 44) indicate a standard deviation of serotype-specific IgG concentration of around 1 on the natural logarithmic scale, at all ages. For serious adverse reactions in Block 1, 26 subjects will be allocated to the post-neonatal PCV group 2 and 26 to the control group 3. This comparison will allow proportions of adverse events of e.g. 10% in the control group versus 48% in the treated group, or 5% vs 40%. If no serious adverse events occur in the first 26 treated children, it is likely that the true adverse event rate is 10% or less (and similarly in Block 2 for neonatal PCV group 1). Given 70% seroprotection (>0.5g/ml) after 1 dose of PCV at age 6 weeks (43), the sample size of 100 per group (min. 90 evaluable) allows this proportion to be estimated with 95% CI of 60-79% and will have 80% power at the 5% significance level to detect a 20% difference from group 1 (i.e. 90%) or group 3 (i.e. 50%).

For ALRI hospital admissions, assuming a rate of 0.0425 per child month under 1 year, a 50% decrease in either vaccinated group compared with controls is detectable. We can detect differences in carriage rates between the groups from 1 month onwards of say 40% down to 22% or lower.

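### The declared primary comparison (neonatal PCV versus control) uses no data from the 1-month group, so it cannot answer Aim 2, and the sample size was worked out for other contrasts

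*Protocol*

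**What the plan says.** Aim 2 (Aims of the Study) asks: "Does neonatal immunization with PCV provide a more favourable antibody response in early childhood than immunization starting at 1 month of age, without compromising safety". The heading of question 2 in section vi repeats that comparison of neonatal with early infant immunization.

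Under question 2 the protocol names its primary outcome and comparison: "For our primary outcome, serum Pnc serotype-specific IgG antibody at age 2 months will be compared between neonatal PCV and control groups". Group 3 is the arm labelled Control in Table 1, and it receives no PCV. The next sentence says that this will assess the following: "booster antibody response to the second dose of PCV in the neonatal group compared to infants given their first dose at 1 month of age". It names naturally acquired antibody in controls as a further comparator. The same paragraph adds: "We note that a safe and equally immunogenic outcome would be a more favourable response to neonatal PCV".

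Section vii states: "The sample size requirements were based on the primary questions and assumed 80% power and a 5% significance level". It takes 70% seroprotection after one PCV dose as the reference, with 100 infants per group and at least 90 evaluable, and claims 80% power "to detect a 20% difference from group 1 (i.e. 90%) or group 3 (i.e. 50" per cent). Section viii bases the principal analyses on t-tests and chi-square tests.

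**The concern.** Three places in the current text point to different primary contrasts:

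- the declaration in section vi: group 1 v group 3;
- Aim 2, the question 2 heading and the sentence after the declaration: group 1 v group 2, with control as a further comparator in that sentence;
- the power statement in section vii: group 2 v group 1, or group 2 v group 3.

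A significant difference between groups 1 and 3 would show that two PCV doses raise antibody at 2 months above no PCV. It would not show that starting at birth does better than, or as well as, starting at 1 month. With two candidate primary contrasts in the text, the one reported as primary could be settled after the data are seen.

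A second gap follows. The protocol counts equal immunogenicity as a favourable result, but it states no margin. A non-significant t-test or chi-square test does not establish equality.

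**Working it through.** **Inputs.** Reference rate 70%, alternatives 90% and 50%, 90 evaluable per group, 5% level (section vii; sidedness is not stated, two-sided assumed). SD of log IgG: the published responses "indicate a standard deviation of serotype-specific IgG concentration of around 1 on the natural logarithmic scale, at all ages". Block table: 104 per group in total; Block 1 puts 26 infants in group 2 and none in group 1.

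**Formula (two proportions, pooled variance under the null).**
Power = Φ{ [ |p1 − p2| − 1.96 × √(p̄(1 − p̄)(1/n1 + 1/n2)) ] / √( p1(1 − p1)/n1 + p2(1 − p2)/n2 ) }

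**1. The plan's own figures.**
- 70% v 50%, n = 90: p̄ = 0.60; null SE 0.0730; alternative SE 0.0715; (0.20 − 1.96 × 0.0730)/0.0715 = 0.795; power **78.7%**. At n = 100 it is 82.8%.
- 90% v 70%, n = 90: p̄ = 0.80; null SE 0.0596; alternative SE 0.0577; (0.20 − 1.96 × 0.0596)/0.0577 = 1.440; power **92.5%**.
- The exact 95% interval for 70/100 is 60.0% to 78.8%, which matches the stated 60-79%.

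The statement of 80% power reproduces, with 70% v 50% as the limiting case.

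**2. Group 1 v group 2 on concurrently randomised infants.** Outside Block 1, group 2 has 104 − 26 = 78 infants. At the same evaluable fraction, 78 × 90/104 = 67.5 against 90 in group 1. Then p̄ = 0.814, the null SE is 0.0626 and the alternative SE 0.0641; (0.20 − 1.96 × 0.0626)/0.0641 = 1.205; power **88.6%**.

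**3. The declared primary, group 1 v group 3.** The protocol gives no figure. With control at 50% and n = 90:

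| Assumed group 1 rate | Power |
|---|---|
| 60% | 26.9% |
| 65% | 53.0% |
| 70% | 78.7% |
| 75% | 94.0% |
| 80% | 99.1% |
| 90% | above 99.9% |

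On the log scale with SD 1, the ratio of geometric means detectable with 80% power is exp[(1.96 + 0.84) × √(2/90)] = exp(0.418) = 1.52.

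**4. If group 1 v group 2 is meant as non-inferiority.** n per group = (1.96 + 0.84)² × 2 × 0.70 × 0.30 / margin², for true rates of 70% in both groups, one-sided 2.5% and 80% power. The margins are illustrative assumptions; the protocol gives none.

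| Margin (points) | n per group |
|---|---|
| 10 | 330 |
| 15 | 147 |
| 20 | 83 |

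Solving for the margin at n = 90 gives 2.80 × √(0.42/90) = 0.191, about 19 points.

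**The case against.** The strongest defence is that the trial is introduced as proof of principle for the safety and immunological feasibility of neonatal PCV, ahead of larger studies. A comparison with unvaccinated infants at 2 months addresses that directly, and the protocol links it to earlier protection. This stands: group 1 v group 3 is a legitimate primary test and should stay.

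Nor is the Aim 2 contrast left out. Section vi mentions it and section vii powers it. That also stands, and it limits the point to which contrast is designated primary. It does not remove the conflict between the declaration and the sentence after it.

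A reader might infer that the declared primary is almost certain to be positive. The documents do not support that. It pairs the 90% and the 50%, which section vii offers as separate detectable alternatives to 70%, not as joint expected rates. The protocol itself warns that maternal antibody may make neonatal responses look modest, and step 3 shows how far power then falls.

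A reader might also infer that the Aim 2 contrast is adequately powered without qualification. That holds for a superiority difference of about 20 points: 80% v 70% has about 34% power at 90 per group, and step 4 shows the limits under non-inferiority.

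Two cautions apply to the remedy. At 2 months group 1 has had two PCV doses and group 2 one (Table 1), so the contrast mixes timing with dose number, and Aim 2 speaks of early childhood more broadly. Nor does a fixed sequence over two contrasts say how the seven vaccine serotypes share the 5%; an analysis plan may settle that.

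**Conclusion.** The inconsistency is real and sits in the current text. The declared primary test cannot do what the next sentence says it will do, does not answer Aim 2, and is not one of the contrasts for which section vii gives power. Naming the Aim 2 contrast costs little in power under the protocol's own superiority assumption: 92.5% at 90 per group, or 88.6% on concurrent infants. If equal immunogenicity is the claim, the existing sample supports only a margin near 20 points.

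These figures rest on a two-sided 5% test (one-sided 2.5% for non-inferiority), 90 evaluable per group, and a 70% rate taken from one dose at 6 weeks in another population. The protocol gives no observed 2-month rate for neonatally vaccinated or control infants in PNG, so power for group 1 v group 3 can only be shown as a range.

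**What to change.** - **Section vi, question 2.** Keep group 1 v group 3 on serotype-specific IgG at 2 months as the proof-of-principle test. Name group 1 v group 2 at 2 months as the second primary comparison, each tested at 5% in that fixed order. State that at 2 months this compares two doses with one. Correct the sentence that now credits the control comparison with assessing the 1-month group.
- **Hypothesis.** Say whether group 1 v group 2 tests superiority or non-inferiority. If non-inferiority, state and justify the margin, add to section viii an analysis that compares a confidence interval with it, and state what the existing sample can show.
- **Section vii.** Restate power by contrast at 90 evaluable per group: 92.5% for 90% v 70% (about 88-89% on concurrent infants), 78.7% for 70% v 50%, and a range for group 1 v group 3 by assumed neonatal rate.

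Cost: wording in three sections, with no extra infants or samples for the superiority reading or for a margin near 20 points. A tighter margin would need more infants. The headline claim would then also depend on the harder contrast, and group 1 v group 2 could be tested formally only if group 1 v group 3 succeeds.

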### Table 1. Neonatal Immunization with Pnc Conjugate Vaccine Study Outline

|  | Birth | 1 -3wk | 1mth | 2mths | 3mths | 4mths | 6 mths | 9mths | 10mths | 18mths |
| --- | --- | --- | --- | --- | --- | --- | --- | --- | --- | --- |
| Group 1 Neonatal PCV | HepB, BCG, OPV, PCV |  | DTP/Hib, HepB, OPV, PCV | DTP/ Hib, OPV, PCV | DTP/ Hib, OPV, HepB |  | Measles | PPV Measles |  |  |
| Group 2 Infant PCV | HepB, BCG  OPV |  | DTP/Hib, HepB, OPV, PCV | DTP/Hib, OPV, PCV | DTP/Hib, OPV, HepB, PCV, |  | Measles | PPV Measles |  |  |
| Group 3 Control | HepB, BCG  OPV |  | DTP/Hib, OPV, HepB | DTP/Hib, OPV | DTP/Hib, OPV, HepB |  | Measles | PPV Measles |  |  |
| Nose Swab |  | weekly | X |  | X |  |  | X |  | X |
| Saliva 1-2 ml |  |  | X | X | X | X |  | X | X | X |
| Serum 2-4 ml | **X*** |  |  | X | **X** | **X** |  | **X** | **X** | **X** |
| PBMC 3-5ml | **X*** |  |  |  | **X** |  |  | **X** | **X** | **X** |
| Morbidity surveillance |  |  |  |  |  |  |  |  |  |  |

HepB: hepatitis B vaccine; PCV: 7-valent Pnc-CRM197 conjugate vaccine; OPV: oral polio vaccine; DTP: diphtheria-tetanus-whole-cell pertussis; Hib: *Haemophilus influenzae* type b tetanus toxoid conjugate vaccine (PRP-T); PPV: 23-valent Pnc polysaccharide vaccine

***** Cord blood sample: total 10ml taken for PBMC (peripheral blood mononuclear cells)

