# Immunization schedule and follow-up

Village reporters will inform study staff if a woman has delivered outside hospital. A study nurse will visit the delivery ward at Goroka Hospital at least once daily to identify newborns to enrolled women. Following recruitment, infants will be randomized to one of three equal-sized groups to receive: 1) PCV at ages 0-1-2 months, 2) PCV at ages 1-2-3 months and 3) no PCV. Birthweight and weight at each follow-up visit will be recorded. Routine infant immunizations will be given in accordance with the PNG schedule (Table 1). As PCV has not been evaluated in this population previously, the first 52 infants will be randomized to groups 2 or 3 only, and the safety data will be reviewed by an independent safety monitoring committee. Conjugate Hib vaccine (ActHib), which is mixed with DPT, has recently been introduced into the immunization schedule in PNG, after being shown to be safe and immunogenic in this population when given at ages 1, 2 and 3 months (76). Since it is in short supply, we may have to purchase it. BCG and DPT/Hib are routinely administered in the deltoid muscle. Hepatitis B and measles will be given in the right thigh. PPV (at 9 months) and PCV will be given in the left thigh.

All immunizations will be given either in Goroka Hospital or at the PNGIMR clinic. Following immunization, children will be monitored at the clinic for 2 hours. Children will then be seen 1 and 2 days after each dose during primary immunization and on day 7 following PPV to check for local or systemic reactions. Children will be seen weekly by nursing staff to age 4 weeks. Guardians will be informed of time of appointments and transport to Goroka clinic will be arranged. If they fail to attend their appointment, we will make 3 further attempts to bring the children for routine follow-up. Guardians may choose to remove their child from the study at any time. Participants will cease to be in the study if they suffer an allergic reaction to vaccination or have inadvertently been given routine immunizations by someone other than the study nurses. All such children will continue to receive medical attention from clinic and field staff as required.

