# **iv) Specimen collection**

This study will involve collection of cord blood and a total of 6 blood samples over the first 18 months of life (3 samples before 6 months). Nurses at PNGIMR have extensive experience in venepuncture for culture and immunogenicity studies in young infants (5, 76). Preparation of PBMCs also allows for collection of 1.5-2ml plasma, which will be defibrinated and used for serological assays (IgG subclasses, OMP IgG) if insufficient serum is collected. This has been validated in our laboratory and defibrinated plasma is the source for the WHO pneumococcal QC sera. All specimens will reach the laboratory within 2 hours.

*Serum* (2-4ml) will be taken at birth (cord), 2, 3 and 4 months of age (initial responses to 1, 2 and 3 doses of PCV), 9 and 10 months (pre- and post-PPV booster) for memory to PCV serotypes, and for antibody persistence at 18 months.  Pnc serotype-specific IgG antibodies in serum will be measured on all samples. CPS IgG and IgG subclasses will also be measured. *Heparinised blood* (3-5ml) will be collected for T-cell cytokine studies from cord blood and at 3, 9, 10 and 18 months of age to examine development of Pnc and vaccine-specific immunity as well as overall development of Th1/Th2 immunity. This amount of blood has proven sufficient in previous studies by our group (65) for the assays proposed.

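### The 2-month IgG compares two PCV doses with one and with none; it cannot show that the second dose in the neonatal group produced a booster response

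*Protocol*

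**What the plan says.** The dose times are "1) PCV at ages 0-1-2 months, 2) PCV at ages 1-2-3 months and 3) no PCV" (Immunization schedule and follow-up).

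The primary outcome for the neonatal question is stated in section vi, question 2: "For our primary outcome, serum Pnc serotype-specific IgG antibody at age 2 months will be compared between neonatal PCV and control groups". The next sentence attaches an interpretation to it: "This will assess whether there is a booster antibody response to the second dose of PCV in the neonatal group", judged "compared to infants given their first dose at 1 month of age and to naturally acquired antibody levels in the control group". The text then adds that the result will settle whether neonatal PCV protects earlier.

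On sampling, section iv says serum "will be taken at birth (cord), 2, 3 and 4 months of age (initial responses to 1, 2 and 3 doses of PCV". It counts, besides cord blood, "a total of 6 blood samples over the first 18 months of life (3 samples before 6 months". The serum row of Table 1 reads "Serum 2-4 ml | X* | | | X | X | X": the cells for 1-3 weeks and for 1 month are empty. The CPS IgG row of Table 2 likewise has no entry at 1 month.

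**The concern.** A booster response to a second dose is a response larger than the same dose would give in an unprimed infant. To see it, one needs either the level just before that dose or an arm that shows what the first dose leaves on its own. Group 1 has neither. Its 2-month IgG is a single number that mixes maternal and naturally acquired antibody, whatever the birth dose induced, and the response to the 1-month dose.

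Whether a birth dose primes or blunts later responses is central to this trial. The background section on neonatal immunization cites hyporesponsiveness after one neonatal Hib conjugate, and the safety monitoring board is asked to look for tolerance or immune suppression. Two misreadings are possible:

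- simple accumulation could be reported as boosting;
- a weakened second response could pass unnoticed at 2 months because antibody from the first dose makes up the difference. Question 2 also treats equal immunogenicity as a favourable outcome.

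**Working it through.** **1. Doses received before each serum sample.** This assumes that blood is drawn before the dose at the same visit, which the label of 1, 2 and 3 doses in section iv itself requires.

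| Serum | Group 1 (0-1-2) | Group 2 (1-2-3) | Group 3 |
|---|---|---|---|
| Cord | 0 | 0 | 0 |
| 2 months | 2 | 1 | 0 |
| 3 months | 3 | 2 | 0 |
| 4 months | 3 | 3 | 0 |

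The label in section iv fits group 2 only. No group 1 sample follows exactly one dose. The text, Table 1, Table 2 and the count of three samples before 6 months (2, 3 and 4 months) agree on this. Cord serum is no substitute for a pre-dose level: it precedes both doses and carries maternal antibody, which question 2 itself names as a disturbance: "Though neonatal responses to PCV may appear modest because of maternal antibody present, conjugate vaccines may still prime for memory".

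**2. What the two contrasts estimate.** Group 1 versus group 3, the named primary contrast, is two doses versus none. Group 1 versus group 2 is two doses versus one. Neither isolates the birth dose.

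**3. The plan's own figures.** Section vii gives an SD of about 1 on the natural-log scale, 100 per group (minimum 90 evaluable), 80% power and 5% significance (taken here as two-sided). Power for 70% versus 50% seroprotection comes to 78.7% at n=90 and 82.8% at n=100. For 70% versus 90% it is 92.5% and 94.8%. The exact 95% CI around 70% at n=100 is 60.0-78.8%. The stated figures reproduce, and this point does not affect them.

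**4. Illustration with no boosting.** Let C be background antibody, D0 what the birth dose leaves at 2 months, and D1 the increment from the 1-month dose. All three are assumed, because the protocol gives none of them. Without boosting:

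- group 1 = C + D0 + D1, and group 2 = C + D1
- ratio = 1 + (D0/D1) / (1 + C/D1)
- z = ln(ratio) / (1 × √(2/n)), with √(2/100) = 0.1414 and √(2/90) = 0.1491

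| D0/D1 | C/D1 | n | Ratio | ln | z | Chance of p<0.05 (noncentral t / normal) |
|---|---|---|---|---|---|---|
| 0.25 | 0 | 100 | 1.25 | 0.223 | 1.58 | 34.9% / 35.1% |
| 0.5 | 0 | 100 | 1.5 | 0.405 | 2.87 | 81.4% / 81.8% |
| 1 | 0 | 100 | 2.0 | 0.693 | 4.90 | 99.8% / 99.8% |
| 0.25 | 1 | 90 | 1.125 | 0.118 | 0.79 | 12.3% / 12.4% |
| 0.5 | 1 | 90 | 1.25 | 0.223 | 1.50 | 31.9% / 32.2% |
| 1 | 1 | 90 | 1.5 | 0.405 | 2.72 | 77.2% / 77.6% |

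**5. The named primary contrast.** Take a birth dose that does nothing (D0 = 0) and a 1-month dose that only doubles background (D1 = C). Group 1 over group 3 is then (C + 0 + C)/C = 2.0, z = 0.693/0.1491 = 4.65, and the chance of significance at n=90 is 99.6%. There is no second-dose boost in this scenario.

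**6. Masked blunting.** Take C = 0, D0 = 0.25 of a one-dose increment, and a second response cut by 20%. Group 1 over group 2 is 0.25 + 0.80 = 1.05, ln = 0.049, z = 0.33 at n=90, and the chance of significance is about 6%. The groups would look equal.

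**The case against.** The strongest reply is that the protocol frames the booster as a between-group comparison at a fixed age and defines no individual booster responder. A reader might infer that the plan fails because no group 1 infant can be scored; the documents do not support that, since no such score is proposed. The reply does not rescue the interpretation, because the between-group contrasts are two doses versus one and two versus none, and each mixes accumulation with boosting.

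A reader might also infer that a 2-month excess would necessarily be reported as boosting, with high probability. That goes too far. How often it could happen depends on the birth-dose residual and the background, neither of which is given. The zero-background figures are the upper end, and question 2 itself warns that neonatal responses may look modest.

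Third, the 2-month level does serve the other stated purpose. Whether antibody is higher earlier can be answered whatever the mechanism. That stands.

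Fourth, priming and blunting are examined elsewhere: the PPV challenge at 9-10 months, avidity maturation at 4, 9 and 10 months, T-cell assays, and the safety board's review. Sera matched for dose number also exist (group 1 at 2 months with group 2 at 3 months), though at different ages. So it would be wrong to say that blunting must go undetected in this trial. What stands is that the 2-month IgG cannot carry the booster claim made for it.

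**Conclusion.** The point holds as a limit on interpretation. The sentence attached to the primary outcome claims something the sampling cannot deliver: at 2 months, boosting by the second dose cannot be told apart from accumulation of two doses. This follows from the sampling and dose times alone and concerns all 104 infants planned for group 1 (52 in Block 2 and 52 in Blocks 3-4).

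The size of the risk is illustrative. With no boosting, the chance of a significant group 1 versus group 2 difference runs from about 12% to over 99% across the assumed residuals and backgrounds. This rests on an additive model, an SD of 1 on the log scale, and a two-sided 5% test of one serotype.

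A reader might conclude that the primary outcome or the sample size is invalid. Neither follows: the endpoint, the test and the power figures stand, and the trial remains able to show whether antibody is higher at 2 months. The label in section iv is a plain misstatement for group 1.

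**What to change.** No new blood draw is needed.

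1. In section vi, question 2, replace the booster statement. Say that the 2-month IgG compares antibody levels after two doses begun at birth with levels after one dose at 1 month and after no dose, and that this addresses earlier protection but not boosting.
2. State there that conclusions on priming and memory rest on the 9- to 10-month PPV response already planned under question 3. The 2-month CPS IgG avidity already listed in Table 2 (PCV serotypes 6B, 14 and 19F) may be compared between groups 1 and 2 as supportive evidence only. It too is two doses versus one, and residual maternal IgG may affect it.
3. In section iv, say that the 2-, 3- and 4-month sera follow 1, 2 and 3 doses in group 2 but 2, 3 and 3 doses in group 1.

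The cost is protocol wording and one further comparison of a result already scheduled, subject to the serum-volume limits that section v mentions. The downside is a more modest claim for the 2-month result.
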